## Abstract

**Background:**

Subcortical ischemic vascular cognitive impairment (SIVCI) is the most common form of vascular cognitive impairment. Importantly, SIVCI is considered the most treatable form of cognitive impairment in older adults, due to its modifiable risk factors such as hypertension, diabetes mellitus, and hypercholesterolemia. Exercise training is a promising intervention to delay the progression of SIVCI, as it actively targets these cardiometabolic risk factors. Despite the demonstrated benefits of resistance training on cognitive function and emerging evidence suggesting resistance training may reduce the progression of white matter hyperintensities (WMHs), research on SIVCI has predominantly focused on the use of aerobic exercise. Thus, the primary aim of this proof-of-concept randomized controlled trial is to investigate the efficacy of a 12-month, twice-weekly progressive resistance training program on cognitive function and WMH progression in adults with SIVCI. We will also assess the efficiency of the intervention.

**Methods:**

Eighty-eight community-dwelling adults, aged > 55 years, with SIVCI from metropolitan Vancouver will be recruited to participate in this study. SIVCI will be determined by the presence of cognitive impairment (Montreal Cognitive Assessment < 26) and cerebral small vessel disease using computed tomography or magnetic resonance imaging. Participants will be randomly allocated to a twice-weekly exercise program of (1) progressive resistance training or (2) balance and tone training (i.e., active control). The primary outcomes are cognitive function measured by the Alzheimer’s Disease Assessment Scale-Cognitive-Plus (ADAS-Cog-13 with additional cognitive tests) and WMH progression.

**Discussion:**

The burden of SIVCI is immense, and to our knowledge, this will be the first study to quantify the effect of progressive resistance training on cognitive function and WMH progression among adults with SIVCI. Slowing the rate of cognitive decline and WMH progression could preserve functional independence and quality of life. This could lead to reduced health care costs and avoidance of early institutional care.

**Trial registration:**

ClinicalTrials.gov NCT02669394. Registered on February 1, 2016

**Supplementary Information:**

The online version contains supplementary material available at 10.1186/s13063-021-05156-1.

## Introduction

Worldwide, one new case of dementia is detected every 4 s [1]. Cerebrovascular disease, such as stroke, is the second most common cause of dementia after Alzheimer’s disease (AD) [2–5], accounting for up to 38% of all dementia cases [6]. Much of stroke research to date has focused on overt ischemic strokes. However, covert ischemic strokes may outnumber overt strokes by five to one, and approximately 25% of people over 80 years of age have one or more silent brain infarcts [7]. Consequently, the prevention of covert ischemic stroke is now a recognized research priority [8].

Vascular cognitive impairment (VCI) encompasses all levels of cognitive decline, from mild cognitive deficits to dementia, due to both overt and covert cerebrovascular disease [9]. The most common cause of VCI is cerebral small vessel disease, in which covert ischemic damage to the brain leads to the development of subcortical ischemic vascular cognitive impairment (SIVCI) [10–12]. In SIVCI, cerebrovascular damage predominantly manifests as white matter hyperintensities (WMHs) of presumed vascular origin and lacunes. Symptoms include prominent impairment in processing speed and executive functions, but can also include impaired memory, language, and visuospatial functions [13, 14]. Functional impairments such as gait disturbance, unsteadiness, and frequent, unprovoked falls are also present [15]. Overall, the clinical consequences of covert ischemic strokes are substantial.

Fortunately, SIVCI may be the most treatable form of cognitive dysfunction in older adults because its key risk factors, which include hypertension, diabetes mellitus, and hypercholesterolemia, are modifiable. Exercise is a promising approach to delay the progression of SIVCI [16–20], as it can effectively modify key cardiometabolic risk factors [16–20], improve vascular function, and alter response during ischemia [21, 22]. Middleton and colleagues [23] demonstrated in the Canadian Study of Health and Aging cohort that physical activity reduced the risk of SIVCI. A cross-sectional study of 1238 people with no history of overt stroke found that those in the highest quartile of physical activity were almost 50% less likely to present evidence of covert stroke compared to those who reported no regular weekly exercise [24].

However, the best type of exercise intervention for persons with SIVCI is unknown. Broadly, the two most common forms of exercise training are (1) aerobic training (e.g., running) and (2) resistance training (e.g., lifting weights). Current research efforts in SIVCI and exercise focus primarily on aerobic training [25, 26] despite evidence that suggests resistance training has important benefits for cardiometabolic health [27–30], cognitive function [31–34], and notably, WMH progression [35, 36]. Resistance training may also benefit individuals with SIVCI by directly moderating muscle loss (i.e., sarcopenia) whereas aerobic exercise does not. Sarcopenia is a risk factor for impaired mobility and falls [37], which are associated with WMHs [15, 38, 39]. Preliminary evidence suggests that resistance training may be beneficial for people with SIVCI. A 12-month randomized controlled trial (RCT) with community-dwelling older women showed progressive resistance training (PRT) significantly improved executive functions [32] and slowed WMH progression [35], compared with an active control group [35].

The mechanisms by which resistance training may promote cognitive function are not well established. One potential mechanism is through the upregulation of neurotrophic factors such as brain-derived neurotrophic factor (BDNF), vascular endothelial-derived growth factor (VEGF), and insulin-like growth factor-1 (IGF-1) [40, 41]. These neurotrophic factors are thought to mediate the beneficial effects of exercise on brain plasticity and cognitive function [40, 41]. Notably, resistance training is especially effective for increasing levels of serum IGF-1 in older adults [33]. IGF-1 in the periphery can pass through the blood–brain barrier where it is involved in vascular maintenance and remodeling [42]—reductions in IGF-1 are associated with decreased cerebral vascular density and blood flow [43]. IGF-1 is also associated with increased myelination [42], which may reduce the progression of white matter damage. Overall, evidence suggests that resistance training may be particularly protective for people with SIVCI.

Therefore, we propose a proof-of-concept, single-blind RCT to primarily examine the efficacy of a 12-month, twice-weekly PRT program to improve cognitive function and reduce WMH progression in community-dwelling adults with SIVCI. The secondary objective is to assess the effect of PRT on regional brain volumes, white matter integrity, myelin content, functional connectivity, specific cognitive processes, physical performance, cardiometabolic risk factors, sleep, physical activity, mood, quality of life, blood biomarkers, and cortisol from saliva. The tertiary objective is to explore the underlying mechanisms by which PRT may promote cognitive function.

## Methods

### Design

We will conduct a 12-month, parallel group, proof-of-concept RCT of 88 community-dwelling adults with SIVCI, aged 55 years and older. Participants will be randomly assigned to receive 12 months of (1) twice-weekly PRT or (2) twice-weekly balance and tone training (BAT; active control). There will be three measurement points occurring at baseline, 6 months, and 12 months conducted by blinded assessors (Fig. 1). The experienced research team will implement standardized protocols and train study personnel (Fig. 2).

**Fig. 1 Fig1:**
[figure not shown]
Overview of study design from recruitment to study completion

**Fig. 2 Fig2:**
[figure not shown]
Schedule of enrolment, interventions, and assessments according to the SPIRIT Checklist

### Recruitment

We will recruit adults with SIVCI through general newspaper advertisements and four clinics: (1) University of British Columbia (UBC) Hospital Clinic for Alzheimer Disease and Related Disorders, (2) Vancouver General Hospital (VGH) Stroke Clinic, (3) VGH Falls Prevention Clinic, and (4) VGH Geriatric Internal Medicine Teaching Clinic. Individuals that appear eligible will be mailed an information package regarding the study, including a consent form. Those that are interested will be invited to a screening and consent session. This session will involve the administration of (1) the Physical Activity Readiness Questionnaire [44] to assess physical readiness for exercise and (2) the Mini-Mental State Examination (MMSE) [45] and Montreal Cognitive Assessment (MoCA) [46] to assess cognitive function. When a participant reports a relevant health concern or condition (e.g., arterial fibrillation), they will be provided a form to be completed by their family physician to confirm their current health status and suitability to start an exercise program (Fig. 1).

### Time frame

Participant enrollment began on May 17, 2016, and the final assessment is anticipated to be completed by March 2022. The COVID-19 pandemic impeded recruitment for much of 2020. As of October 24, 2020, 69 individuals (78% of the target sample) have been recruited and randomized.

### Eligibility

#### Inclusion criteria

We will include community-dwelling adults who fulfill the criteria for SIVCI, defined as the presence of cognitive impairment [46] combined with cerebral small vessel disease [47]. Cognitive impairment will be operationalized as a MoCA score < 26 [46], and cerebral small vessel disease will be defined as the presence of WMHs and/or lacunes on computed tomography (CT) or magnetic resonance imaging (MRI) [47]. Additional inclusion criteria require the participant to: (1) be 55 years or older; (2) have an MMSE score > 20 [45]; (3) be community-dwelling (i.e., living in their own homes) in metro Vancouver; (4) be able to comply with scheduled visits, treatment plan, and other trial procedures; (5) read, write, and speak English with acceptable visual and auditory acuity; (6) be on a fixed dose of cognitive medications that is not expected to change during the 12-month study period, or, if they are not on any of these medications, they are not expected to start them during the 12-month study period; (7) provide informed consent; (8) be able to walk independently; and (9) must be in sufficient health to participate in the PRT program.

#### Exclusion criteria

We will exclude individuals who: (1) have an absence of cerebral small vessel disease on a brain CT or MRI; (2) are diagnosed with dementia of any type or another type of neurodegenerative or neurological condition (e.g., Parkinson’s disease); (3) are diagnosed with a genetic cause of SIVCI; (4) are at high risk for cardiac complications during exercise and/or unable to self-regulate or to understand the recommended activity level; (5) participated in regular resistance training in the last 6 months; (6) have clinically important peripheral neuropathy or severe musculoskeletal or joint disease that impairs mobility; (7) recently started taking medications (< 3 months prior to study) that may negatively affect cognitive function, such as anticholinergics; (8) are planning to participate, or already enrolled in, a clinical drug trial or exercise trial concurrent to this study; or (9) are unable to meet MRI scanning requirements, as specified by the UBC 3T MRI Research Center.

### Sample size calculation

Power analyses were conducted in G*Power 3.1 [48]. We have sized this trial to allow the evaluation of PRT on the Alzheimer's Disease Assessment Scale-Cognitive-Plus (ADAS-Cog-Plus) [49] and WMH progression at trial completion; WMH progression is considered a valid surrogate marker in therapeutic trials of SIVCI [50]. The ADAS-Cog-Plus is the original ADAS-Cog-13 with additional measures of executive functions and verbal fluency, and it is more sensitive to subtle cognitive changes than the original ADAS-Cog-13 or ADAS-Cog-11 [49]. Our prior 6-month RCT of aerobic exercise on cognitive function, as measured by the ADAS-Cog-11, in adults with SIVCI observed an effect size of 0.89 (Cohen’s *d*) in the complete-case analysis [51]. We also demonstrated twice-weekly PRT slowed WMH progression in older women; the effect size observed was 0.60 (Cohen’s *d*). Based on this effect size of 0.60, assuming an alpha of 0.05 (two-tailed) and a beta of 0.20, 35 participants per group will provide a power of 0.80 [48]. We are aiming to recruit a total of 88 participants with SIVCI (i.e., 44 participants per group), which will accommodate a conservative 20% drop-out rate.

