#### Treatment allocation

##### Randomization

Participants will be randomly assigned (1:1) to either the 12-month, twice-weekly PRT program or the 12-month, twice-weekly BAT program. The randomization sequence will be generated and held by a central web-based randomization service. Permuted blocks of varying sizes will be used to ensure balance over time.

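### The stated 80% power at 35 per group does not follow from the stated two-tailed inputs, which give about 70%

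*Protocol article*

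**What the plan says.** The Sample size calculation section says "Power analyses were conducted in G*Power 3.1" and does not name the test chosen there. It cites two earlier effects: 0.89 for cognition (ADAS-Cog-11, an aerobic exercise trial, complete cases) and 0.60 for white matter hyperintensity (WMH) progression (a resistance training trial in older women). Only the second is used for sizing: "Based on this effect size of 0.60", and then "assuming an alpha of 0.05 (two-tailed) and a beta of 0.20, 35 participants per group will provide a power of 0.80".

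The recruitment target follows: "We are aiming to recruit a total of 88 participants with SIVCI (i.e., 44 participants per group), which will accommodate a conservative 20% drop-out rate". The Randomization section gives equal allocation: "Participants will be randomly assigned (1:1) to either the 12-month, twice-weekly PRT program".

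The sample size section mentions no baseline-outcome correlation, covariate gain or repeated-measures gain.

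**The concern.** Every input to a standard two-group calculation is printed, so the result can be checked directly. Two-sided 5% with 80% power at d = 0.60 calls for about 45 per group, and 35 is well short of that.

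What is at stake is how a null WMH result will be read. Readers would take it as coming from a comparison with a one-in-five chance of missing the planning effect, when on the stated inputs the chance is about three in ten. The drop-out margin is also affected. It is presented as a reserve on top of adequate power, but nearly all 44 per group would have to be retained just to come close to 80%.

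**Working it through.** **Inputs** (all from Sample size calculation, except allocation, which is from Randomization)

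- Effect d = 0.60
- Alpha 0.05, two-tailed
- Beta 0.20, so target power 0.80
- Evaluable n = 35 per group
- Target 44 per group, 20% drop-out
- Allocation 1:1

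**Method.** Two-sample t-test with n per group: df = 2n − 2 and noncentrality δ = d·√(n/2). Two-sided power = P(|T| > t_crit), where T is noncentral t with df and δ.

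**Step 1: the plan's own figure, two-sided.** With n = 35, df = 68, δ = 0.60·√17.5 = 2.510 and t_crit = 1.995. Power = **0.697** (normal approximation 0.709). The stated 0.80 is not reproduced.

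**Step 2: n needed for 80%, two-sided.** The normal approximation gives n = 2(1.960 + 0.842)²/0.60² = 43.6, so 44. Exact t results:

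| n per group | Two-sided power at d = 0.60 |
|---|---|
| 35 | 0.697 |
| 44 | 0.795 |
| 45 | 0.804 |

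The exact requirement is 45 evaluable per group. With 20% loss, 45/0.8 = 56.25, so 57 randomised per group, or 114 in total.

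**Step 3: what does give 35?** For a one-sided test at 0.05, t_crit = 1.668 and power at n = 35 is **0.7996**, which rounds to 0.80. The one-sided normal approximation gives n = 2(1.645 + 0.842)²/0.60² = 34.3, so 35. The exact t calculation strictly needs 36 (0.809).

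**Step 4: other explanations.**

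- *Rounding of d.* At n = 35, d = 0.65 gives only 0.764. Power of 80% requires d = 0.679.
- *The other effect size.* d = 0.89 needs 21 per group two-sided and gives 0.956 at 35. The text ties the 35 to 0.60.
- *Baseline adjustment.* If 0.60 were an unadjusted effect and adjustment removed a fraction r² of the variance, the required n would scale by (1 − r²). Reaching 35 needs r = √(1 − 35/45) = 0.47. Assumed values of r = 0.3, 0.4 and 0.5 give power 0.737, 0.770 and 0.815. No r is stated.
- *Repeated measures.* The WMH quantification section schedules MRI at baseline and 12 months only, so WMH volume has one follow-up value and gains nothing from the 6-month visit.

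**Step 5: drop-out step.** 35/0.8 = 43.75, so 44 per group. This is correct. In reverse, 88 × 0.8 = 70.4, or about 35 per group.

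**Step 6: an adjusted level (assumption).** The Primary outcomes section counts improvement in either outcome as evidence of efficacy. If each outcome were tested at two-sided 0.025, power at n = 35 and d = 0.60 would be 0.588, the detectable d at 80% would be 0.75, and 55 per group would be needed.

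**The case against.** The arithmetic itself is hard to dispute. The best case on the other side concerns how much it matters.

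- **The one-tailed origin is conjecture.** The article says two-tailed and names no test, and the exact one-sided requirement is 36, not 35. This stands. The source is a likely explanation, and the error does not depend on it.
- **A null trial means missing both outcomes.** The 30% miss probability belongs to one outcome at d = 0.60. If 0.60 held for both outcomes and they were independent, the chance of at least one success would be 1 − (1 − 0.697)² = 0.91 at unadjusted 0.05. Assumed correlations of 0.3 and 0.5 between the two test statistics give about 0.87 and 0.84. At 0.025 each, the three figures are about 0.83, 0.78 and 0.75. For cognition, the quoted 0.89 would give ample power. This stands as a limit on the consequence. It does not rescue the sentence, which claims 0.80 for the 0.60 calculation. The 0.89 is also weak support, since it comes from another exercise type, a shorter version of the scale and complete cases.
- **The planned model adjusts for baseline**, so its power may exceed 0.70. That is possible, but the effect of 0.60 is already for progression, so any further gain is uncertain, and the section claims none.
- **This is a proof-of-concept trial**, with 69 of 88 randomised by October 2020, and no analysis changes. That argues against enlarging the trial, not against correcting the figure.

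**Conclusion.** The concern holds. On the stated inputs, 35 evaluable per group gives about 70% two-sided power for d = 0.60, roughly 10 percentage points below the claim. The type II error is 0.30, or 1.5 times the stated 0.20. The effect detectable with 80% power is 0.68, and 45 evaluable per group would be needed for 0.60.

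This rests on a two-group comparison of means with no covariate gain, which is all the section describes. The 30% miss probability applies to a single outcome at the planning effect, in practice WMH progression, and not to the either-outcome rule. The figures at 0.025 are ancillary, and the finding does not depend on them.

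**What to change.** Keep the target of 88 and correct the statement in the Sample size calculation section. Suggested wording:

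> With about 35 evaluable participants per group (44 randomised, 20% loss), a two-sided test at 0.05 has about 70% power for a standardised difference of 0.60, or 80% power for a difference of 0.68.

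Two additions:

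- Give the matching figure at whatever level each primary outcome will be tested. If that is 0.025, it is 59% power for 0.60, or 80% power for 0.75.
- If a gain from baseline adjustment is to be claimed, state the assumed baseline-outcome correlation and its source, and say whether the 0.60 is an unadjusted effect. A correlation of about 0.47 would be needed for 35 per group to reach 80%.

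The cost is a wording change and a less favourable stated power. No extra participants are needed and the analysis does not change.

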### Data entry

No personal identifiers will be acquired during data collection. All paper-based data will be stored in locked cabinets and all alphanumeric data will be entered by a trained study personnel who will conduct range checks for data values. All alphanumeric data will be stored on a secured server hosted by the University of British Columbia. All data will be deidentified.

### Measurements

#### Descriptors

Body mass will be measured in kilograms using a calibrated digital scale and height in centimeters using a wall-mounted stadiometer. General health, medication use, and socioeconomic status will be ascertained using questionnaires. The Functional Comorbidity Index [52] will be used to estimate the degree of comorbidity associated with physical functioning.

#### Primary outcomes

The study will be powered based on expected changes in cognition and WMH progression. Improvement in either outcome is considered evidence of efficacy.

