### Statistical analyses

The analyses will follow the intention-to-treat principle (i.e., all individuals will be analyzed according to their group allocation regardless of compliance). We will evaluate between-group differences (PRT vs. BAT) in ADAS-Cog-Plus and WMH volume, adjusted for baseline score, using mixed linear models. Restricted maximum likelihood estimation will be used in order to include all randomized participants to estimate treatment effects, regardless of loss to follow-up. Time since baseline (6 months versus 12 months) will be considered as a repeated variable and will be included as a fixed effect in addition to group and group-by-time interaction. Baseline score on the outcome variable and participant baseline characteristics will be included as fixed covariates. The intercept will be specified as a random effect. Primary and secondary outcomes will be analyzed using this same analytic model.

The intention-to-treat analysis will be followed by a complete-case analysis, in which only participants with valid data at all time points will be included. Moreover, we will compare participants in the PRT group who are compliant with the intervention (defined as attending at least 60% of the total exercise sessions) with the BAT group.

To explore underlying mechanisms, we will assess the association between changes in cognitive function with changes in: (1) neuroimaging outcomes; (2) cardiometabolic risk factors; (3) blood biomarkers; and (4) saliva biomarkers.

The economic evaluation will examine the efficiency of the 12-month PRT program compared with BAT. The outcome of our cost–utility analysis is the incremental cost–utility ratio (ICUR): ICUR = ∆Cost/∆ quality-adjusted life years (QALYs); QALYs, estimated from the EQ-5D-5L, represent time spent in given health states [85, 86].

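### An either-or success rule over two primary outcomes is paired with one undivided alpha of 0.05 and no multiplicity control

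*Protocol article*

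**What the plan says.** The Methods part of the Abstract and the Primary outcomes section give two co-equal primaries: change in ADAS-Cog-Plus and WMH progression. Primary outcomes then sets the success rule: "Improvement in either outcome is considered evidence of efficacy".

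Sample size calculation says the trial is sized for both outcomes. It gives the only alpha in the document: "assuming an alpha of 0.05 (two-tailed) and a beta of 0.20, 35 participants per group will provide a power of 0.80". The number rests on the WMH effect ("Based on this effect size of 0.60"). For cognition, an earlier aerobic-exercise trial that "observed an effect size of 0.89" on the ADAS-Cog-11 is cited, but it does not drive the number. The recruitment target is 88, or 44 per group, to allow for 20% drop-out.

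Statistical analyses specifies a mixed linear model and adds: "Primary and secondary outcomes will be analyzed using this same analytic model". It gives no test level, and no order, split or gate between the two primaries.

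**The concern.** The rule is a union: one win out of two is enough. Two chances at the full alpha do not give a 5% chance of a false-positive primary result. The trial would report efficacy from a criterion looser than the single alpha on the page suggests, and a win on one outcome could be presented while the other shows nothing.

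The Abstract and Introduction make efficacy the primary aim, and the Discussion ties establishing efficacy to exercise prescription. The error rate behind that claim should therefore be known and stated. It also cannot be repaired convincingly once the results are seen.

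**Working it through.** **Inputs.** From the article: two primaries; success on either; alpha 0.05 two-tailed; d = 0.60; 35 evaluable per group; 20% drop-out; 1:1 allocation. Assumed: the correlation ρ between the two test statistics, taken from 0 to 0.9. Also assumed: each outcome is tested at 0.05, because the undivided alpha implies it and nothing else is given.

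**The plan's own figure.** For two means, n per group = 2(z₁₋α/₂ + z₁₋β)²/d².

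- Two-tailed 0.05: 2(1.960 + 0.842)²/0.36 = 43.6, so 44 (45 by noncentral t).
- One-tailed 0.05: 2(1.645 + 0.842)²/0.36 = 34.4, so 35 (36 by noncentral t).
- Drop-out: 35/0.80 = 43.75, so 44 per group and 88 in total, as stated.

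The drop-out step reproduces. The figure of 35 does not follow from the stated two-tailed alpha. At 35 per group, two-tailed power is Φ(0.60·√(35/2) − 1.960) = Φ(0.550) = 0.71 (0.70 by noncentral t), not 0.80. That is a separate error, but it sets the baseline for the power cost below.

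**Error rate of the either-or rule.** With c = 1.960:

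- Any false-positive primary: 1 − P(|Z₁| < c, |Z₂| < c). At ρ = 0 this is 1 − 0.95² = 0.0975.
- False claim of benefit only: 1 − P(Z₁ < c, Z₂ < c). At ρ = 0 this is 1 − 0.975² = 0.0494. For a single outcome it is 0.025.

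Other values of ρ use the bivariate normal distribution.

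| ρ | Any false-positive primary | False claim of benefit |
|---|---|---|
| 0 | 9.8% | 4.9% |
| 0.3 | 9.5% | 4.8% |
| 0.5 | 9.1% | 4.5% |
| 0.7 | 8.3% | 4.2% |
| 0.9 | 7.0% | 3.5% |
| Single outcome | 5.0% | 2.5% |

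The inflation is a factor of 9.75/5 = 1.95 at ρ = 0 and 7.0/5 = 1.4 at ρ = 0.9. In simulation over the same range of ρ, Hochberg brings the familywise rate to between 4.2% and 5.0%.

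**Power cost at 35 evaluable per group, d = 0.60.**

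- One outcome responds. At two-sided 0.025, Φ(2.510 − 2.241) = Φ(0.269) = 0.61 (0.59 by noncentral t), against about 0.70 at 0.05.
- Both respond, ρ = 0, normal approximation. Unadjusted: 1 − (1 − 0.709)² = 0.915. Hochberg: 1 − (1 − 0.606)² + (0.709 − 0.606)² = 0.856.
- Both respond, ρ = 0.5, by simulation: 0.850 unadjusted and 0.78 with Hochberg.

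The chance of at least one win therefore falls from 85–92% to 78–86%. If cognition responded at the cited d = 0.89, power for it would fall only from 0.96 to 0.92 (noncentral t).

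**The case against.** The strongest objection is that the article never says each outcome is tested at 0.05. The figure is a power-calculation input for one effect size, no familywise rate is promised, and the analysis section gives no level. An either-or rule is compatible with full error control, so what is missing could be a procedure held in an analysis plan that is not shown. Part of this stands: the per-test level is an inference, and the figures are conditional on it. But the article itself fixes both the success rule and the only alpha, and read together they give the inflated rate. A procedure held elsewhere would still make the power at 0.05 the wrong figure to state.

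A reader might infer that false claims of efficacy reach about 10%. The documents do not support that. The rule credits improvement only, and the 9.8% counts significant worsening as well. False claims of benefit stay below 5%; what they exceed is the 2.5% that one two-sided test would allow. Nor does a near doubling hold throughout, since it weakens as the correlation rises.

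A reader might also infer that the trial must grow. Holding 80% power for each outcome at 0.025 would take 55 evaluable per group, or 55/0.80 = 69 per group and 138 in total. Error control does not require that: Hochberg or Holm can be applied at 88. For the same reason, the sample size does not prove that no adjustment is intended.

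Finally, this is a self-described proof-of-concept trial with one cognitive and one imaging outcome, and how strict to be is partly a matter of judgement. That lowers the severity. It does not remove the point, because the two outcomes are pooled into a single conclusion about efficacy.

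**Conclusion.** The concern holds in a limited form. Read as written, the plan pairs a union success rule with a single undivided alpha and no multiplicity control. If each primary is tested at two-sided 0.05, the familywise error is above 5% at every correlation examined, from 9.8% at 0 to 7.0% at 0.9. False claims of benefit run from 4.9% down to 3.5%, against 2.5% for one outcome. The result rests on two assumptions: the per-test level, inferred from the sample size section, and the correlation, which the article does not give. Given the proof-of-concept aim, this is a should-fix.

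**What to change.** Keep both primaries and the either-or rule, and add to Statistical analyses:

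- Familywise error across the two primaries is controlled at two-sided 0.05 by Hochberg. If the larger p-value is at most 0.05, both are significant; otherwise only the smaller counts, and only if it is at most 0.025. Holm is an alternative that needs no assumption about dependence.
- A significant difference counts as efficacy only if it favours resistance training.
- Both primary results are always reported together.

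Restate the power in Sample size calculation at the adjusted level. Correct the 0.80 at the same time, because 35 per group does not give it at two-tailed 0.05 even before any adjustment.

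The cost is a few sentences and a registry amendment, which Trial status already commits to for protocol updates. No new data or participants are needed. The loss of power set out in the working should be stated openly. By the article's own dates (version of February 2021, final assessments expected by March 2022), the rule can be settled before the outcomes are complete.
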